#### Intervention

In this trial, there will be two groups, an intervention group (*n* = 70) that will immediately enrol in the Hans Kai program and a control group (*n* = 35) that will access standard care available in the Canadian Province of Manitoba, including any services and programs offered at NorWest, except Hans Kai. There will be no special criteria for discontinuing or modifying allocated interventions, except in cases involving worsening of pre-existing health conditions that may either put participants at risk if they continue the program or hinder their participation in the program. The program that will be the intervention in this trial is the Hans Kai program offered at NorWest, with the only modifications being the trial assessment visits described below. The minimum level of compliance to the intervention is 80%; to remain in the trial, study participants must attend a minimum of six health school sessions.

Participants in the control group will remain as close to a “typical” community member as possible as they will be able to receive any other health programming normally available to them in Winnipeg, except the Hans Kai program. Standard of care will be made available to all members of the control group in compliance with the healthcare rights of Canadians and Manitobans holding a Manitoba health card. NorWest staff will provide support to the community members without a Manitoba health cards in obtaining one. The only deviation from standard care in the control group will be the baseline, 3-month, and 6-month visits described below during which the control participants will complete questionnaires and undergo physical assessments.

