**Fig. 1 Fig1:**
[figure not shown]
Hans Kai holistic model of wellness

The program is structured in two consecutive phases that are designed to promote participant retention and positive long-term health outcomes by improving health competence and decreasing social isolation and loneliness. First, Hans Kai participants attend a set of eight informational sessions, the Hans Kai Health School, that are delivered by healthcare professionals weekly in a group setting to develop the skills necessary to improve their health and wellbeing. The health school includes sessions on a variety of health-related topics, including the determinants of health; setting health goals and developing action plans; health indicators; healthy nutrition, grocery store shopping, and meal planning; physical activity; stress, coping, and health, including sleep; communicable and noncommunicable diseases, including modifiable risk factors; and access to healthcare services and preventive care.

After completing the health school, participants form Hans Kai groups and begin to meet regularly (at least once a month) at times, dates, and locations all determined by the group members, and independently of facilitators. Group size can vary from 5 to 30 members. To be classified as a Hans Kai group, at each meeting, the group members must conduct self-health checks, including blood pressure, blood glucose, and waist circumference measurements; they must also participate in some form of physical activity (e.g., Zumba or yoga), enjoy a healthy snack, and have time to socialize. The supplies for the health checks are provided by NorWest. The groups make all decisions collectively, and as they continue to meet, members may request to facilitators additional educational sessions not discussed in the core health school, or activities of interest of the group members (e.g., discussions on specific health topics, such as stroke or menopause, and cooking classes).

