### Randomized controlled trial

#### Study design

The experimental component of the mixed methods RCT will follow a 6-month 2-group parallel superiority design, with a 12–18-month observational follow-up (see Fig. 2 for details). There will be a 2:1 allocation of participants to the intervention versus the control group. The control group will consist of 6 months of standard care that adults can access in the Canadian Province of Manitoba, including any services and programs that are offered at NorWest, except Hans Kai. At the end of the 6-month control period, the control group participants will be offered the opportunity to join Hans Kai and, once in the intervention, they will be followed for up to 18 months. The participants in the intervention group will be followed for a minimum of 6 months (RCT period) and up to 18 months; however, the randomized controlled portion of the study will last for the first 6 months, while the observational follow-up for them will last 12 months. After baseline, there will be a 2-month period of Hans Kai program implementation during which program participants will attend the Hans Kai Health School, prior to starting regular group meetings.

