#### Randomization

Following the eligibility screening and the baseline assessment visit, participants will be randomly allocated to either the intervention group or the control group using a computer-generated random sequence. After screening and enrollment, once participants are determined to be eligible to participate in the clinical trial, a research team member will press a randomize function within the REDCap secure system. Participants will be assigned with a 2:1 ratio of intervention to control groups. To ensure allocation concealment and minimize bias, randomization will be performed by a third-party biostatistician not affiliated with the research team. The randomization sequence will be uploaded into the University of Manitoba Research Electronic Data Capture (REDCap) system randomization module [26, 27].

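### Staying in the trial depends on attending six health school sessions, a post-randomisation condition that only the intervention arm can fail during the 6-month RCT

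*Protocol article*

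**What the plan says.** The order of events comes from four sections of the protocol article.

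- **Randomization:** "Following the eligibility screening and the baseline assessment visit, participants will be randomly allocated to either the intervention group or the control group".
- **Study design:** after baseline, "there will be a 2-month period of Hans Kai program implementation during which program participants will attend the Hans Kai Health School". For controls, "At the end of the 6-month control period, the control group participants will be offered the opportunity to join Hans Kai".
- **The Hans Kai Program:** "Hans Kai participants attend a set of eight informational sessions, the Hans Kai Health School", held weekly.
- **Intervention:** controls have standard care, "including any services and programs offered at NorWest, except Hans Kai". For the programme, "The minimum level of compliance to the intervention is 80"%, and "to remain in the trial, study participants must attend a minimum of six health school sessions".

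The Intervention section also says that there are no special criteria for discontinuing or modifying the allocated intervention, apart from worsening of pre-existing health conditions.

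The Statistical analysis section compares mean within-subject change from baseline to 6 months between arms, at the 0.05 level. It names no analysis population and says that multiple imputation will handle missing data.

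**The concern.** Attendance is behaviour after allocation, and only one arm has sessions to attend. A rule that ends trial participation for low attenders therefore acts on one side of a comparison that randomisation had balanced. If people who miss sessions differ in prognosis from those who come, the retained intervention group is no longer exchangeable with the full control group. The primary result would then not show whether offering Hans Kai does better than standard care.

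The rule is stated outright, so this is not a detail that the article has left to another document. It also governs data collection: if the 6-month MHC-SF is never obtained from those removed, no later analysis plan can recover it.

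**Working it through.** **1. Which arm can fail the condition.** Randomisation follows baseline. The health school occupies the next 2 months for the intervention arm. Controls have no access to it until 6 months, when the randomised comparison has ended. Only the intervention arm can fail the condition in that window.

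**2. The plan's own detectable difference.** Inputs from the Sample size section: SD of change 5, 60 versus 30 analysed, 80% power. The 0.05 level is from Statistical analysis, taken as two-sided.

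- 60 versus 30: (1.96 + 0.84) × 5 × √(1/60 + 1/30) = 3.13. The plan says 3.1.
- Conservative case, 10 groups versus 30 controls: (1.96 + 0.84) × 5 × √(1/10 + 1/30) = 5.11. The plan says 5.2; the noncentral t gives 5.25.

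Both figures reproduce.

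**3. Bias from one-sided removal.** Let f be the share of the intervention arm removed, and g the amount by which their mean change would have fallen below that of those retained. The whole-arm mean is (retained mean) − f × g, so analysing only those retained overstates the arm by f × g. The documents give neither quantity. The ranges below are assumptions: f from 10% to 25%, and g from 2.5 to 5 points (half to one SD). Here g is a prognostic gap, one that would exist even if the programme did nothing.

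| f | g | Bias f × g | Share of 3.1 | Share of 5.2 |
|---|---|---|---|---|
| 10% | 2.5 | 0.25 | 8% | 5% |
| 10% | 5 | 0.50 | 16% | 10% |
| 20% | 2.5 | 0.50 | 16% | 10% |
| 20% | 5 | 1.00 | 32% | 19% |
| 25% | 2.5 | 0.625 | 20% | 12% |
| 25% | 5 | 1.25 | 40% | 24% |

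**4. Effect on the type I error.** With no true programme effect, the two-sided error is Φ(−1.96 + b/SE) + Φ(−1.96 − b/SE), where b = f × g and SE = 5 × √(1/n₁ + 1/30). Taking n₁ = 70 × (1 − f), with removals as the only loss in that arm and participants independent:

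- f = 10% (n₁ = 63, SE 1.11): 5.6% at g = 2.5 and 7.4% at g = 5.
- f = 20% (n₁ = 56, SE 1.13): 7.3% and 14.3%.
- f = 25% (n₁ = 52.5, SE 1.14): 8.5% and 19.4%.

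**5. Effect on power, if removals come on top of the 15% dropout.** At a 3.1-point difference (t-test), power is 78.3% with 60 versus 30. It falls to 76.8% with 54 (10% removed) and 74.9% with 48 (20% removed). This is small beside the bias.

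**6. Two inconsistencies in the Intervention section.** Six of eight sessions is 6/8 = 75%, and 80% of eight is 6.4 sessions, so an 80% threshold on the health school alone would need seven. Separately, a section that allows no discontinuation criterion except worsening health also sets an attendance condition for staying in the trial.

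**The case against.** The best counter-reading is that the sentence only defines adherence. It follows a statement about minimum compliance, and the Procedure section says that adherence will be monitored by tracking attendance. The article also condenses a fuller protocol, so an as-randomised analysis may be specified elsewhere. This is why the consequences above are conditional. It does not remove the point: the words make attendance a condition of remaining in the trial, and nothing else in the article says that low attenders are still followed or analysed.

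Several stronger readings are tempting, and the documents do not support them.

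- **The rule is shown to favour the programme.** That direction is likely, since poor attenders often do worse, but the article has no data on who misses sessions. They could be busier, healthier people.
- **The bias could reach 1.6 points.** That takes 25% removed and a gap of 6.5, the uncontrolled 6-month gain in the Sample size section. Such a gap assumes that those removed would not change at all. It mixes lost programme benefit, which is a difference in estimand and vanishes under the null, with prognostic selection, which is what inflates false positives.
- **Imputation leaves these people out.** The article does not say so, and their baseline scores exist. The supportable claim is that imputing them under missing-at-random would rest mainly on attenders' outcomes, which is the assumption in doubt.
- **The 15% dropout allowance omits these removals.** Study setting ties the expected 85% to attending the programme as well as completing visits; Ethical considerations uses dropouts for voluntary withdrawals. The article leaves this unclear.
- **75% against 80% is a firm contradiction.** The 80% refers to the intervention, which also includes the group meetings, so it may not be meant for the eight sessions alone. The two figures still need to be related to each other.

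**Conclusion.** The concern holds in conditional form. As written, the article sets a post-randomisation condition for staying in the trial that only the intervention arm can fail before 6 months, and no other section neutralises it. If applied literally, it puts the randomised basis of the primary comparison at risk, and uncollected outcomes cannot be recovered later.

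The size is illustrative: 0.25–1.25 MHC-SF points, with a type I error of 5.6% to 19.4% instead of 5%. It rests on an assumed 10–25% removed, an assumed prognostic gap of 2.5–5 points, the plan's SD of 5, and independence between participants. The direction towards the programme is expected but not documented. The two inconsistencies in the Intervention section are wording problems of lesser weight.

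**What to change.** Delete attendance as a condition of remaining in the trial. State that every randomised participant is assessed to the 6-month visit whatever their attendance, and that the primary analysis includes all participants as randomised. Keep attendance as a descriptive adherence measure and for a supportive complier-average-causal-effect analysis.

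In the same edit:

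- Reconcile the 80% compliance figure with the six-of-eight rule, saying what the 80% is a percentage of.
- Reconcile the attendance rule with the sentence on discontinuation criteria.
- Say whether the 15% dropout allowance includes low attenders.

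The cost is a few protocol sentences and outcome visits for low attenders. The estimate will include people who received little of the programme and so will be somewhat diluted, but it answers the question of offering the programme. The planned size need not change: with everyone followed and 15% lost, the comparison is still about 60 versus 30, with a detectable difference of about 3.1 points under the plan's independence assumption.

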#### Outcomes

All study outcomes will be measured pre- and post-intervention at multiple timepoints and will be assessed using a multi-method approach involving subjective self-report measures and objective indicators (see Table 1 for details). The primary objective of this RCT is to measure the impact of the Hans Kai program on participant mental health using the MHC-SF [24] by comparing the MHC-SF scores obtained by the intervention group with those of the control group. The MHC-SF is a 14-item standardized self-report questionnaire that assesses emotional, social, and psychological wellbeing of respondents by investigating the regularity with which they experience symptoms of positive mental health. This scale shows high internal consistency (*α* = and moderate test–retest reliability, as well as good convergent and discriminant validity when it is used to measure mental wellbeing in Western contexts [23].

**Table 1 Tab1:** Quantitative objectives, outcome measures, and timepoints of assessment

Objectives	Outcome measures	Timepoints of assessment
*Primary objective:*		
To compare the effects of the Hans Kai program versus standard care on mental health	Mental Health Continuum Short Form (MHC-SF)	The MHC-SF will be completed at each assessment visit
*Secondary objectives:*		
1) To compare the effects of the Hans Kai program versus standard care on social connections	1) Revised UCLA Loneliness Scale	The UCLA Loneliness Scale will be administered at baseline and then every 6 months of the Hans Kai program or standard care control
2) To compare the effects of the Hans Kai program versus standard care on health-related knowledge and empowerment (i.e., self-efficacy and self-determination)	2) Perceived Health Competence Scale (PHCS)	The PHCS will be administered at baseline and then every 6 months of the Hans Kai program or standard care control
3) To compare the effects of the Hans Kai program versus standard care on health-promoting behaviors (i.e., diet, alcohol consumption, tobacco use, physical activity, and sleep)	3a) Modified version of the Healthy Eating Assessment 3b) Pittsburgh Sleep Quality Index (PSQI) 3c) Fitbit	All self-report measures will be administered at baseline and then every 6 months of the Hans Kai program or standard care control Participants will be asked to wear a Fitbit for a total of seven days at baseline and then every 6 months of the Hans Kai program or standard care control
*Tertiary objective:*		
To compare the effects of the Hans Kai program versus standard care on clinical measures of cardiometabolic health	Clinical exams will be performed by a registered nurse	Waist circumference, blood pressure, fasting blood sugar, and heart rate will be measured at baseline and then every 6 months of the Hans Kai program or standard care control

The secondary objectives of this RCT involve investigating the impact of the Hans Kai program on social connections, health-related knowledge and empowerment (i.e., self-efficacy and self-determination), and health-promoting behaviors (i.e., diet, alcohol consumption, tobacco use, physical activity, and sleep). To this end, a set of self-report questionnaires as well as objective measures will be used to assess changes in these outcomes over time (see Table 1 for details).

Feelings of loneliness and social isolation (secondary objective 1) will be measured using the revised UCLA Loneliness Scale [29], a 20-item scale designed to measure one’s subjective feelings of loneliness and social isolation. This scale is highly reliable (internal consistency *α* coefficient = 0.89–0.94 and test–retest reliability over a 1-year period *r* = 0.73) and valid in assessing self-reported loneliness and social isolation in adults.

Health-related knowledge and empowerment in the form of self-efficacy and self-determination (secondary objective 2) will be measured using the Perceived Health Competence Scale (PHCS) [30]. This is a standardized measure of general health management self-efficacy beliefs designed to assess respondents’ self-perceived ability to accomplish health-related goals and manage their health positively. The scale has good internal consistency (0.82-0.90) and test–retest reliability (0.82–0.60), as well as demonstrated construct validity.

Change in health-related behaviors (secondary objectives 3 to 5) will be assessed using a combination of objective indicators and subjective measures. Changes in nutritional behavior (diet), alcohol consumption, and tobacco use will be measured using a modified version of the Healthy Eating Assessment [31] that was specifically created for the purpose of this trial. The adapted self-report scale includes 22 items divided into two main sections: a first section that includes 18 items evaluating respondents’ eating habits, and a second section including four items that assess respondents’ alcohol consumption and tobacco use.

The standardized self-report questionnaire Pittsburgh Sleep Quality Index (PSQI) [32] will be used to subjectively measure sleep quality, habits, and patterns subjectively. This scale includes nine items that assess seven aspects of sleep: (1) subjective sleep quality, (2) sleep latency, (3) sleep duration, (4) habitual sleep efficiency, (5) sleep disturbances, (6) use of sleeping medications, and (7) daytime dysfunction over the last month. Scoring varies across items; however, an overall score can be calculated by summing the seven component scores, yielding a Global PSQI score ranging from 0 to 45, with higher scores indicating poorer sleep quality (secondary outcome 6). The PSQI has shown acceptable internal homogeneity, consistency (test–retest reliability), and validity. Additionally, a global PSQI score greater than 5 yield a diagnostic sensitivity of 89.6% and specificity of 86.5% (*k* = 0.75, *p* < 0.001) in distinguishing good and poor sleepers.

Sleep quality (Fitbit sleep score) and length (sleep time) will also be measured objectively using data provided by a Fitbits that participants will wear for 7 days at each assessment point [33]. The average of these seven measurements will be used.

Fitbits will also be used to measure behavioral changes in terms of physical activity (secondary outcome 7) [34, 35]. Specifically, at each assessment point, daily step count and moderate-to-vigorous physical activity will be recorded over a 7-day period, and the average of these seven measurements will be used as an indicator of participants’ level of physical activity.

The tertiary objective of this RCT is to investigate the impact of the Hans Kai program on clinical cardiometabolic health indicators, including blood glucose, waist circumference, body weight, and blood pressure. These indicators will be assessed objectively by a registered nurse who every 6 months will perform a clinical exam of study participants.

#### Procedure

At the baseline assessment, all participants (both the intervention and control group) will undergo a clinical exam that will be performed by a trained research team member, who will measure participants’ blood glucose levels, blood pressure, weight, and waist circumference according to provincial health standard protocols. All clinical measurements will be taken three times, except blood glucose, which will be measured only once using a glucometer that tests capillary blood samples taken by finger prick sampling. Blood pressure will be measured in triplicate following 10 min of acclimatization to the measurement room, with a 2-min break between measurements. The average of the three assessments will be used as measure of blood pressure. Following the clinical assessment, participants will be asked to complete all self-report measures, including a sociodemographic questionnaire, the MHC-SF, the Revised UCLA Loneliness Scale, the PHCS, the Adapted Healthy Eating Assessment, and the PSQI. Fitbits will also be used to objectively assess changes in participants’ physical activity as well as sleep quality and patterns. Participants will be shown by the study staff how to wear the Fitbit and will be given basic instructions on its use. Study participants will be asked to wear the Fitbit for 7 complete days on the assessment week, including when they are asleep so that their sleep quality and patterns can be recorded.

Following the baseline assessment, study participants will be randomly assigned to either the intervention group or the control group (see Fig. 3 for Consort flow diagram) [36]. After random allocation to either trial condition, participants in the intervention group will immediately enter the Hans Kai program, while participants in the control group will be exposed to 6 months of standard care. Participants who are randomized to the control group will receive $100 CAD (made out in two payments of $50 CAD, one at the 3-month visit and one at 6-month visit). This remuneration for participants who are randomly assigned to the control group instead of the intervention group will be used as a strategy to improve adherence to the intervention protocol. We will also monitor adherence by tracking attendance to the health school and trial visits. See Fig. 4 for the SPIRIT flowchart of the schedule of enrollment, intervention, and assessments.

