#### Sample size

The primary analysis will be performed based on the pre- to post-intervention changes in the primary outcome, the Mental Health Continuum Short Form (MHC-SF) [23], comparing the mean change scores between the intervention and control participants, with a nested design to account for participant group membership in Hans Kai [24]. Based on data from previous studies [4, 24] and the RCT study design, we expect the changes from baseline MHC-SF scores within each subject group to be approximately normally distributed with a standard deviation of 5. The average within-group pre-post changes in MHC-SF scores in the Hans Kai prospective cohort study were + 6.5 in 34 participants at 6 months [18]. With a planned sample size that accounts for dropouts of 90 adults, with 60 intervention participants and 30 control participants, we would have a power of 80% to detect a true difference in the mean response of intervention and control participants of − 3.1 or 3.1 at the end of the 6-month RCT component [25]. This scenario assumes that the outcomes of each participant will be independent of the Hans Kai peer group they join. However, since part of the Hans Kai program includes forming groups, a very conservative power calculation considers the “effective” sample size for the Hans Kai program to be equal to the number of groups rather than the number of participants. We anticipate that 60 intervention participants will form 10 independent groups of six participants per group. In this very conservative scenario, with 10 groups in the intervention arm and 30 control participants, we would be able to detect a true difference in the mean scores of intervention and control participants of − 5.2 or 5.2 with 80% power. We believe that the actual study power will fall somewhere between the two scenarios presented here. With a starting sample size of 105 adults and an estimated 15% dropout rate during the study period [18], we expect to generate a minimum sample of approximately 90 participants at the 18-month follow-up.

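### The plan does not say how individually randomised people are assembled into the weekly group class, so any start delay would fall after randomisation and in the intervention arm only

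*Protocol article*

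**What the plan says.** **Allocation.** The Randomization section states: "Following the eligibility screening and the baseline assessment visit, participants will be randomly allocated to either the intervention group or the control group". It adds that, once a person is found eligible, "a research team member will press a randomize function within the REDCap secure system". The Procedure section gives the same order: "Following the baseline assessment, study participants will be randomly assigned to either the intervention group or the control group". The unit is the individual, at a 2:1 ratio (70 intervention, 35 control).

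**Start of the intervention.** The Procedure section says that "participants in the intervention group will immediately enter the Hans Kai program". The Intervention section repeats that this group "will immediately enrol in the Hans Kai program".

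**Form of the programme.** The Hans Kai Program section (text after Fig. 1) describes a first phase of eight sessions "that are delivered by healthcare professionals weekly in a group setting". Each group picks its champion at the last of these sessions. Peer groups may have 5 to 30 members. The Sample size section says: "We anticipate that 60 intervention participants will form 10 independent groups of six participants per group".

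**Clocks.** Study design places a 2-month health school after baseline and names no other interval before group meetings. In the section on the 6-month RCT, the intervention arm's visits are counted from the end of the health school, with the full assessment 6 months later. The control arm's visits are counted from enrolment, with the full assessment at 6 months. The same section then labels the primary outcome visits as 3-month and 6-month in both arms. The Statistical analysis section compares changes from baseline to 6 months.

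**The concern.** A weekly group course has a start date, and people who complete baseline one by one will not all reach it on the day they are allocated. The article says entry is immediate, gives no time for a class to assemble, and describes no mechanism for assembling one.

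If there is a delay, three features make it matter.

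- It comes after allocation is known and affects only the intervention arm.
- It lengthens that arm's time from baseline to final assessment by an amount that differs between people and appears in no stated timeline.
- It leaves room for one-sided loss. The Intervention section makes attendance at six or more health school sessions a condition of staying in the trial, so someone who loses interest before the first session can leave after randomisation. Control participants face no such condition and are paid at their 3- and 6-month visits.

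**Working it through.** **1. The plan's own figures.** The Sample size section gives detectable differences of 3.1 (60 v 30) and 5.2 (10 groups v 30) with SD 5 and 80% power; alpha is 0.05, taken as two-sided. The formula is SD × √(1/n₁ + 1/n₂) × (1.960 + 0.842).

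- 60 v 30: 5 × 0.2236 × 2.802 = 3.13 (3.17 with the t distribution).
- 10 v 30: 5 × 0.3651 × 2.802 = 5.11 (5.25 with the t distribution).

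Both agree with the plan. They do not depend on when classes start, so this point leaves them untouched.

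**2. The clocks without any delay.**

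- Intervention: 2 months of health school + 6 months = 8 months after baseline.
- Control: 6 months after enrolment.

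The 8-month reading is supported by the 0 to 20 month range of the secondary analysis: 2 + 6 + 12 months of follow-up = 20. The arms therefore already differ by 2 months, against an analysis window of baseline to 6 months.

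**3. The clocks with a delay of w months.** The intervention assessment falls at w + 2 + 6 months and the control assessment stays at 6. Each month of delay adds one month to the intervention arm and none to the control arm. Under these anchors the delay does not shorten exposure, because the intervention visit moves with the class.

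**4. How large w might be.** The documents give no accrual period, class size or intake calendar, so this step rests on assumptions: even arrival of 105 people over T months, classes filled only by trial participants, and a class that starts when m intervention participants have gathered. The planned 10 groups imply 70/10 = 7 randomised per group (six is the figure after dropout). At 2:1, that takes 105/10 = 10.5 randomisations.

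The intervention accrual rate is r = 70/T per month. The first entrant waits (m − 1)/r and the mean wait is (m − 1)/(2r).

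| T (months) | r per month | First entrant, m = 7 | Mean wait, m = 7 | Mean wait, m = 5 | Intervention assessment at mean wait, m = 7 | Control |
|---|---|---|---|---|---|---|
| 6 | 11.67 | 0.51 | 0.26 | 0.17 | 8.3 | 6.0 |
| 12 | 5.83 | 1.03 | 0.51 | 0.34 | 8.5 | 6.0 |
| 24 | 2.92 | 2.06 | 1.03 | 0.69 | 9.0 | 6.0 |

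A class of 12 would raise the mean to 0.94 months (T = 12) or 1.89 months (T = 24). If several people are randomised together just before a class, w is close to zero.

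**The case against.** The strongest reply is that no delay appears anywhere in the text. The article says twice that entry is immediate. The Randomization section fixes the unit of allocation but not when the button is pressed relative to a class, so randomising several people just before a health school is consistent with it and would make immediate entry true. Hans Kai is described as an ongoing programme (Study setting), and nothing confines classes to trial participants. The trial may also be presented to existing groups at their own sites (Recruitment), which could bring people in together. The six per group refers to peer groups, and no class size is given. Class scheduling is a detail an article may leave to the full protocol, and the design figures are not shown.

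Much of this stands. A delay is an inference and its size is an assumption.

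Three parts do not stand.

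- Separating the class from the peer group is weak: each group chooses its champion at the last health school session, so people moving through together is the natural reading.
- An ongoing programme does not by itself remove a delay, because an eight-session course still has start dates. As an illustration, one continuous stream of 8-week classes would give waits of 0 to 8 weeks, about 4 on average.
- The unequal anchors are stated text, not an omission, and they are why any delay would fall on one arm's clock alone.

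**Conclusion.** The point holds as a gap in the plan that is cheap to close. The article combines individual allocation, immediate entry and a group-delivered first phase without saying how they fit together. Any delay would add one-for-one, in the intervention arm only, to an interval that is already about 8 months against 6. On the stated assumptions (about seven per class, trial participants only, even arrival) the mean wait is about 0.3 months for 6 months of accrual, 0.5 for 12 and 1.0 for 24. It could be near zero with batching.

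A reader might infer more, and the documents do not support it.

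- *That intervention participants do wait while a class fills.* No accrual rate, class size or intake rule is given, and batching is not excluded.
- *That a delay would cut into exposure.* Under the present anchors it lengthens the interval instead. It would shorten exposure only if visits were counted from randomisation and the delay were left in place.
- *That about nine people must be randomised before a class of six can start.* This takes a peer-group size after dropout as the class size and assumes no other attendees.
- *That the arms are mismatched in calendar time.* Both are drawn 2:1 from the same stream and are balanced in expectation, apart from any delay itself.

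No effect of a delay on MHC-SF scores or on dropout can be derived from the documents.

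**What to change.** In the Randomization and Procedure sections, describe intake cohorts:

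1. Complete baseline for a whole cohort within a short window. Sizes divisible by three keep the ratio exact: 9 gives 6 + 3, 12 gives 8 + 4, 15 gives 10 + 5.
2. Randomise the whole cohort 2:1 in one session shortly before its health school starts.
3. Use that date as time zero for the 3- and 6-month visits in both arms, and reconcile Study design, the section on the 6-month RCT and Statistical analysis with it.

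If enrolment is already batched, one sentence saying so settles the first two steps. The common time origin is still needed.

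**Cost.** The change needs protocol wording and a REDCap list blocked by intake cohort. Some volunteers will wait, and a few may leave, before randomisation, where this does not bias the comparison. With a common origin, the 6-month visit falls after about 6 − 2 = 4 months of group meetings in the intervention arm. The team should confirm that this is the contrast it wants; whatever elapsed time it chooses must be the same in both arms.
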